### Statistical analysis

The mediator models assume that the predictor variable causes changes in the mediator variable, and the mediator variable then causes changes in the outcome variable. Mediation analysis will be conducted to evaluate whether the effect of GDM plus PS-UI on long-term UI is mediated through alteration in levels of all assessed parameters. The patient flow will be summarised using a diagram while social-demographic and obstetrics baseline characteristics will be reported as mean and standard deviation for continuous variables and count for categorical variables.

Multivariate logistic regression analyses will be conducted to identify the mediator variables and the outcome (UI 12-month C-section post-partum) that will be changed by the predictor variable (GDM plus PS-UI) as an independent variable after adjusting for confounders. Clinically important covariates will be investigated as potential confounders whenever appropriate for each outcome. There is likely to be missing data that will likely with the duration of the follow-up. The multiple imputations will be used to handle missing data [63]. Results will be expressed as odds ratio [OR], 95% confidence intervals and associated *p*-values. For all tests, the level of significance will be set at a p-value < 0.05. Assessment of the functional, morphological, biochemical, and molecular mediator variables are presented in Table 3.

**Table 3 Tab3:** Statistical tools will be used for the study

	Variables	Statistical methods
Clinical data		
Incidence of UI 12-month post-partum	Categorical	Multivariate analysis, odds ratio and 95% of the Confidence interval
ISI Questionnaire	Categorical	Chi-square test with corrections
PFM: Vaginal muscle contraction pressure; digital vaginal evaluation and US	Categorical	Chi-square test with corrections
RAM: US and Electromyography	Categorical	Chi-square test with corrections
Laboratorial data		
Comparison of serum concentration of CCL7; relaxin; calcium; parathyroid hormone; calcitonin; Vitamin D and Insulin	Continuous	Repeated Measures t-test or one-way analysis of variance (ANOVA) and Area under the curve
Laboratory assays of RAM sample		
Morphological assay Pathological, morphometric, immunohistochemical and ultrastructural	Continuous	ANOVA followed by Tukey’s multiple comparison tests for the normally distributed variables
	Categorical	Chi-square test with corrections

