**Discussion:**

To our knowledge, this will be the first study to provide data on the prevalence of PS-UI and RAM and PFM physical and biomolecular muscle profiles after C-section in mothers with GDM. The longitudinal design allows for the assessment of cause-effect relationships between GDM, PS-UI, and PFMs and RAMs myopathy. The findings may reveal previously undetermined consequences of GDM.

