### GDM plus PS-UI and clinical-biomolecular muscle profile as a long-term predictor of UI

GDM during pregnancy and its association with PS-UI and a specific PFM or RAM biomolecular muscle profile constitute a new triad leading to long-term UI after C-section. We hypothesize that UI 12 months after C-section will be higher in women who developed GDM plus PS-UI compared to women without these factors. Our secondary hypotheses are: (1) GDM plus PS-UI is an independent risk factor for UI development 12 months after C-section and (2) Hyperglycemic-related myopathy parameters are potential mediators of the association between GDM plus PS-UI and symptomatic UI 12 months after C-section.

Therefore, we aim to quantify the clinical-biomolecular muscle profile of PFM and RAM hyperglycemic myopathy during pregnancy in GDM women with PS-UI as exposure, on UI 12 months after C-section and compare the profile to that obtained from women who did not have GDM or PS-UI. We include an analysis of the mediators and moderator variables that are related to PFMD and UI in this evaluation (Fig. 2).

The primary and secondary research questions to be addressed in this research are:

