### Follow-up

All recruited patients will be evaluated as follows: visit − 2- at 34 to 38 weeks gestational age (T2) and inclusion in the C-section delivery cohort (beginning of phase 2). After visit − 3-within 24 and 48 h postpartum (T3), visit − 4- 6 weeks postpartum (T4), and 6 and 12 months postpartum (T5 and T6, respectively). Four cohorts will be followed-up based on the results of GDM and PS-UI diagnosis: (i) GDM plus PS-UI; (ii) GDM without PS-UI; (iii) Non-GDM plus PS-UI and (iv) Non-GDM without PS-UI.

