### Sample size

It is not possible to calculate the sample size for Phase 1 of the recruitment. All eligible pregnant women will be invited to be included in this phase. Considering that the incidence of UI was higher at 24-months in GDM-positive C-section post-partum women (44.8%) as compared with women without GDM (18.4%) [5], assuming a two-sided confidence level of 95% and power of 80%, it will be necessary to follow-up 49 C-section post-partum women in each purposed cohort to identify at least a 22% difference between them. Considering a 20% loss in follow-up, we will include 59 women in each cohort, which means that 236 women will be included in this research.

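### The 12-month UI regression and mediation analysis use one composite predictor, GDM plus PS-UI, so an effect of PS-UI alone would make it significant with no effect of GDM

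*Protocol article*

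**What the plan says.** **Cohorts.** Under Follow-up in the protocol article, "Four cohorts will be followed-up based on the results of GDM and PS-UI diagnosis": both conditions, GDM only, PS-UI only, and neither. Sample size sets 59 women per cohort, 236 in all.

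**Primary hypothesis.** The last part of the Background states that "UI 12 months after C-section will be higher in women who developed GDM plus PS-UI compared to women without these factors". The Primary question repeats this contrast.

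**Model.** Statistical analysis describes multivariate logistic regression to find the mediators and the 12-month outcome "changed by the predictor variable (GDM plus PS-UI) as an independent variable after adjusting for confounders". The mediation analysis in the same section takes the same composite as its exposure. Neither sentence names a reference group.

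**Predictors.** The Predictor variables section lists GDM and PS-UI as two predictors, and Assessment procedures and instrumentation speaks of GDM and/or PS-UI. Neither statement becomes a separate model term for 12-month UI.

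**Definitions.** PS-UI is any leakage that first appears in pregnancy. The outcome is any involuntary leakage. Women with UI before pregnancy are excluded.

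**Intended conclusions.** The abstract says "The longitudinal design allows for the assessment of cause-effect relationships between GDM, PS-UI, and PFMs and RAMs myopathy". The secondary hypotheses call the combination an independent risk factor acting through hyperglycemic myopathy. The main Discussion frames the findings as long-term UI after GDM exposure.

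**The concern.** The composite holds two exposures, and one of them is the outcome symptom at an earlier time. The Background itself describes PS-UI as a risk factor for UI two years after C-section. A positive association between the composite and 12-month UI is therefore expected whether or not GDM contributes. Adjustment for confounders does not help, because PS-UI is inside the exposure.

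The study could then report that GDM plus PS-UI is an independent risk factor, with mediation through hyperglycemic myopathy, when GDM has no effect and there is no joint effect. The four cohorts contain the information needed to tell these cases apart, but the stated model does not use it.

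**Working it through.** **Inputs from Sample size.** Planning rates are 44.8% (GDM) and 18.4% (no GDM). The test is two-sided at 5% with 80% power, and "it will be necessary to follow-up 49 C-section post-partum women in each purposed cohort".

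**Reproducing the 49.** Pooled-variance formula, with mean p = (0.448 + 0.184)/2 = 0.316:

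n = [1.960·√(2·0.316·0.684) + 0.842·√(0.448·0.552 + 0.184·0.816)]² / 0.264² = (1.289 + 0.531)² / 0.0697 ≈ 47.5, so 48.

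The stated 49 is reproduced to within one woman. It fits the 26.4-point gap between the planning rates. The 22-point difference quoted beside it would need 67 to 72 per group; that is a separate matter and is not used here.

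**The composite contrast when GDM does nothing.** The documents give no UI rate by GDM and PS-UI jointly, so the risks below are assumptions. Each cohort has 49 evaluable women. Both PS-UI cohorts share risk p1, and the two cohorts without PS-UI share risk p2.

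Power = Φ{[(p1 − p2) − 1.960·√(2p(1−p)/49)] / √[(p1(1−p1) + p2(1−p2))/49]}, where p is the mean of p1 and p2.

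For 44.8% v 18.4%: (0.264 − 1.960·0.0939)/0.0901 = 0.887, and Φ(0.887) = 0.81. The odds ratio is (0.448/0.552)/(0.184/0.816) = 3.60.

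| UI risk with PS-UI | UI risk without | P(both v neither significant) |
|---|---|---|
| 40% | 18% | 0.67 |
| 40% | 15% | 0.80 |
| 45% | 18% | 0.83 |
| 50% | 15% | 0.97 |
| 50% | 10% | 0.996 |

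**If the reference is the other three cohorts pooled.** Their risk is (2·18.4 + 44.8)/3 = 27.2%. The odds ratio is 2.17, and the test is significant in 62-63% of studies. The problem does not depend on which reference group is meant.

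**Separate terms on the same women.** These figures come from 2,000 simulated studies per scenario with 49 per cohort. The GDM column is from a logistic model with GDM and PS-UI as separate terms. The interaction column is from the same model with the product added.

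| Truth | Both v neither | GDM term | Interaction |
|---|---|---|---|
| PS-UI acts alone | 81% | 4% | 4% |
| GDM acts alone | 81% | 98% | 5% |
| Only the doubly exposed cohort is raised | 82% | 59% | 43% |

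Both v neither gives the same answer in all three cases. The GDM term separates the first two. The 98% agrees with the two-proportion formula for 98 v 98 women (0.98).

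**Precision at a mean risk of 30%** (variance 0.21; detectable difference = 2.8 × SE):
- One pair of cohorts, 49 v 49: SE = √(2·0.21/49) = 0.0926, detectable 26 points.
- GDM effect pooled over PS-UI, 98 v 98: SE = √(2·0.21/98) = 0.0655, detectable 18 points. The SE is 29% smaller (1 − 0.0655/0.0926).
- Additive interaction: SE = √(4·0.21/49) = 0.131, detectable 37 points.

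**The case against.** The strongest defence is that the hypothesis concerns the combination, so both v neither answers the question asked. The protocol also names two predictors and forms four groups for the primary outcome, and an analysis plan that is not shown might enter separate terms. Part of this stands: nothing in the article rules such terms out. But the regression and the mediation analysis as written both take the composite as the exposure. A plan that follows that text keeps the defect, so this is a stated choice and not merely omitted detail.

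Four stronger readings are tempting, and the documents do not support them:

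- **Half the sample is excluded.** A reader might infer this from the both-versus-neither question. The regression sentence names no reference group, and no text removes the single-exposure cohorts.
- **The study will report a GDM effect.** Strictly, the result would be reported for the combination. The attribution to GDM comes from the abstract, the hypotheses on hyperglycemic myopathy and the Discussion, not from an analysis rule.
- **UI at 12 months in the exposed women is mostly persistence.** The protocol gives no rate of resolution or recurrence for PS-UI. It supports only that exposure and outcome are the same symptom at two times.
- **Table 3's ANOVA with Tukey has the same fault.** With four groups, Tukey gives all six pairwise contrasts, including GDM v no GDM within each PS-UI stratum. A factorial ANOVA would be more efficient, but that is a preference.

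**Conclusion.** The concern holds for the 12-month UI regression and its mediation analysis. If PS-UI alone raises the risk of UI, the composite is significant with probability 0.81 when the protocol's own rates are assigned to PS-UI. The range is about 0.67 to 0.996 over assumed risks of 40-50% with PS-UI and 10-18% without. When GDM alone acts, the probability is also 0.81, so the contrast cannot distinguish the two. It can support a statement about the combination, but not the conclusions about GDM, hyperglycemic myopathy or cause and effect.

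These figures rest on assumed cell risks, 49 evaluable women per cohort and no covariate adjustment. The logical point does not depend on them. At the planned size the main effects can be separated, but a pure interaction is not well powered (43% in the scenario above).

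**What to change.** In Statistical analysis:

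1. Fit one logistic model for 12-month UI to all four cohorts, with GDM, PS-UI and GDM × PS-UI as separate terms plus the planned confounders. This agrees with the Predictor variables section.
2. Report the GDM effect within each PS-UI stratum and pooled over strata, and the PS-UI effect, each with a 95% CI. With the product in the model, the GDM coefficient alone refers to women without PS-UI, so the pooled effect must be averaged over the strata.
3. Report the additive interaction (interaction risk difference or RERI) with a 95% CI, and state that the study is not powered for it.
4. Enter GDM and PS-UI as separate exposures in the mediation analysis.
5. Keep both v neither as the overall contrast, name its reference group, and draw GDM or joint-effect conclusions only from the GDM and interaction estimates.

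The cost is analysis wording, settled before the outcome data are analysed. No further women, visits or measurements are needed.

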### Data measurement

#### Digital palpation and vaginal squeeze pressure

For the digital vaginal evaluation, the examiner will follow the Messelink et al. orientation [55]. A perineometer value higher than 33.6 mmHg will be considered as normal based on our previous nulliparous women study [5].

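### Table 3 fixes continuous muscle measures as categorical, leaves the serum row open to readings that do not test cohort by visit, and sets 0.05 for all tests with no stated control across candidate mediators

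*Protocol article*

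**What the plan says.** All of this is in the protocol article.

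- **Muscle measures (Table 3).** The rows "PFM: Vaginal muscle contraction pressure; digital vaginal evaluation and US" and "RAM: US and Electromyography" are both typed Categorical, with a chi-square test and unspecified corrections.
- **How they are measured (Data measurement).** Pressure is read in mmHg. Pelvic floor ultrasound gives two diameters, hiatal area and levator thickness at rest, contraction and Valsalva. Rectus ultrasound gives thickness. Electromyography is a sampled signal. The only cut-point is for pressure: "A perineometer value higher than 33.6 mmHg will be considered as normal".
- **Schedule (Table 2).** Digital palpation, ultrasound and electromyography are marked at T1, T2, T4, T5 and T6. Squeeze pressure has no row of its own. The laboratory row is marked at all six times and contains five of the seven serum analytes of Table 3 (insulin, PTH, calcitonin, calcium, vitamin D). CCL7 and relaxin are not in it.
- **Serum (Table 3).** The method is "Repeated Measures t-test or one-way analysis of variance (ANOVA) and Area under the curve".
- **Error level (Statistical analysis).** "For all tests, the level of significance will be set at a p-value < 0.05". Mediation is to be examined for every parameter assessed. Tukey tests appear in the continuous tissue-assay rows, and transcriptomics uses an adjusted p-value.

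**The concern.** The second secondary question asks which mediators are abnormal in women with both GDM and PS-UI, and the muscle measures are the main evidence in living women. Cutting a measured quantity into categories discards information in a sample whose size is already fixed. Without cut-points for ultrasound and electromyography, the categories could also be chosen after the data are seen. The text itself speaks of mediation through changes in levels, which a categorical analysis does not use.

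For serum, four cohorts followed over up to six visits raise the question of whether the course differs by cohort. A paired t-test compares two visits and takes no account of cohort. A one-way ANOVA handles either cohort or visit, and takes no account of the correlation within a woman if her visits enter as separate values.

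A 0.05 level applied to a long list of candidates, with no control across the list, also makes an isolated positive finding hard to interpret.

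**Working it through.** **1. The planned size.** Inputs from Sample size: 44.8% against 18.4%, two-sided 5%, power 80%. The pooled normal formula without continuity correction is n = [1.96√(2p̄q̄) + 0.842√(p₁q₁ + p₂q₂)]² / (p₁ − p₂)², with p̄ = 0.316. It gives 47.5, so 48, which agrees with the stated 49 to within one woman. I use 49 evaluable women per cohort below.

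**2. Cost of categorising, two cohorts, 0.5 SD** (assumed: normal data, equal SD, cut at the pooled median).

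- Continuous: power = Φ(0.5·√(49/2) − 1.96) = Φ(0.515) = 69.7%.
- Median split: the proportions are Φ(−0.25) = 0.401 and Φ(0.25) = 0.599. Power = Φ[(0.197·7 − 1.96·√0.5) / √(2·0.401·0.599)] = Φ(−0.006) = 49.8%.
- The asymptotic efficiency of a median split is 2/π = 0.637, so 49 women carry about the information of 31.

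**3. Other cut positions.** Here the difference is 0.566 SD, which has 80% power at 49 per cohort if analysed as continuous. Cuts are placed on the reference cohort, and the other cohort is shifted upwards.

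| Reference cohort below the cut | Power | n per cohort for 80% |
|---|---|---|
| 50% | 59% | 81 |
| 70% | 59% | 80 |
| 80% | 55% | 89 |
| 90% | 44% | 116 |
| 20% | 40% | 130 |
| 10% | 27% | 211 |

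With four cohorts of which one is shifted by 0.566 SD (3,000 simulated trials), ANOVA has 84% power and chi-square on a median split 59%. With no difference, both reject in about 4% to 5% of trials. Chi-square on a fixed cut is therefore valid but inefficient.

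**4. Serum row.** Simulation of 4 cohorts × 49 women × 6 visits, 2,000 runs, with an assumed equal correlation ρ between visits.

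| Reading of the row | ρ = 0.3 | ρ = 0.5 | ρ = 0.7 |
|---|---|---|---|
| One summary per woman, ANOVA across cohorts: type I error | 4.9% | 5.2% | 5.8% |
| All visits pooled as independent, ANOVA across cohorts: type I error | 38% | 55% | 64% |
| One-way ANOVA over visits in one cohort, 0.3 SD shift at one visit: power | 14% | 9% | 3% |
| Repeated-measures ANOVA, same shift: power | 37% | 54% | 76% |

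The summary used was the woman's mean over visits, standing in for an area under the curve. The first and last readings are sound. The summary per woman compares overall level and does not test cohort by visit.

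**5. Number of candidates.** Counting each Table 3 entry once gives 7 serum analytes plus 5 muscle measures (pressure, digital evaluation, pelvic floor ultrasound, rectus ultrasound, electromyography), so 12. For independent null tests at 0.05, the chance of at least one false group difference is 1 − 0.95¹² = 46%. It passes 50% at 14 tests (51%). If ultrasound dimensions and tissue measures are counted separately and the list reaches 30, it is 1 − 0.95³⁰ = 79%, with 30 × 0.05 = 1.5 expected. Positive correlation would lower the percentages but not the expected number.

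These are chance group differences. If a mediator must pass both paths at 0.05 and both are null and independent, the rate per candidate is 0.05² = 0.0025, or 1 − 0.9975³⁰ = 7% over 30. The 79% is approached only if one path is real and almost always detected for every candidate.

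**The case against.** Four points deserve weight.

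- **Serum.** The row names the area under the curve, and the words about repeated measures may be meant to govern the ANOVA as well as the t-test. Either reading gives a sound analysis. A reader might infer that the plan pools six visits as independent and so runs an error rate of 38% to 64%. No section says so. Nor does the plan imply dropping women who miss a visit, because multiple imputation is planned. Six visits are documented for only five of the seven analytes. What stands is that the row is ambiguous.
- **Multiplicity.** A reader might infer that false mediators are likely, or that nothing but transcriptomics is adjusted. The article does not support either. Mediation is defined as two links, and mediators are also to be examined by mediation analysis and adjusted logistic regression. Tukey and the chi-square corrections give some control. However, Tukey acts between cohorts within one variable, the corrections are undefined, and neither acts across mediators. Detail may sit in Additional file 1 or an analysis plan, neither of which is shown. The 0.05 rule for all tests is nevertheless stated here.
- **Categorising.** Digital palpation is graded, so a categorical analysis suits it. The position of any cut in this population is unknown, so the power figures are illustrations.
- **Reach.** The primary question is analysed by logistic regression and does not depend on these rows.

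**Conclusion.** The categorisation point stands on what Table 3 fixes and is the strongest part. Quantities measured on continuous scales are to be tested by chi-square, with a cut-point for only one of them. Under normality and a median split, a 0.5 SD difference at 49 per cohort is detected about 50% of the time instead of 70%. Less central cuts mostly cost more.

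The serum row needs clarifying. It admits a valid summary per woman, and also tests that do not address cohort by visit for the five analytes with six scheduled visits.

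On multiplicity, the text applies 0.05 to all tests over every assessed parameter and states no control across candidate mediators. The size of the consequence is uncertain: 46% for at least one chance group difference among 12 independent null measures, and for 30 candidates from 7% to 79% depending on whether one mediation path is real. None of these should be read as the chance of a false mediator in this study.

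The change should be made before analysis. It affects the secondary, mechanistic aims only.

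**What to change.** - **Muscle measures.** Retype squeeze pressure, ultrasound dimensions and electromyography as continuous (log scale if skewed). Where they are repeated, use a linear mixed model with cohort, visit and their interaction and a random effect for woman. Keep an ordinal or chi-square analysis for digital palpation. Show the 33.6 mmHg cut descriptively.
- **Serum.** Either use the same mixed model, or state that one area under the curve per woman is compared across the four cohorts, and over which visits. State the visits for CCL7 and relaxin.
- **Multiplicity.** Control the false discovery rate at 5% within each mediator family (serum, pelvic floor, rectus clinical, rectus tissue), or label the mediator screen exploratory. Say what the chi-square corrections are.

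Cost: wording and slightly more programming, with no new data. False discovery rate control lowers power for a single candidate. For the muscle measures, the continuous scale recovers some power; for serum and most tissue variables, already treated as continuous, nothing offsets the loss. Labelling the screen exploratory avoids that loss but weakens what can be claimed.

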### Patient and public involvement

The development of the research questions and outcome measures was performed based on previously published clinical research and from our prior translational studies. Patients and the public will not be involved in the study design, recruitment, and the conduct of the study. The patients involved in this study are those admitted to the University Hospital-Botucatu Medical School-UNESP. After completion of the data analysis, we plan to introduce the results into our routine practice of long-term follow-up care. We are also planning to translate the results into short and easy-to-read summaries to disseminate it to the relevant patient community groups through local media.

